**Table 3. Number of events, accumulated person-time, and HRs for cancer associated with eczema severity, Denmark**

|                    | N | events | P-Y
at
risk | Rate
per
1,000 | Hazard ratio and 99%
confidence interval  |                    |
|--------------------|---|--------|-------------------|----------------------|----------------------------------------------------------|--------------------|
|                    |   |        |                   |                      | Unadjusted                                               | Mediation
model |
| Any cancer         |   |        |                   |                      |                                                          |                    |
| Unexposed          |   |        |                   |                      |                                                          |                    |
| Exposed – moderate |   |        |                   |                      |                                                          |                    |
| Exposed – severe   |   |        |                   |                      |                                                          |                    |
| Lung cancer        |   |        |                   |                      |                                                          |                    |
| Unexposed          |   |        |                   |                      |                                                          |                    |
| Exposed – moderate |   |        |                   |                      |                                                          |                    |
| Exposed – severe   |   |        |                   |                      |                                                          |                    |
| Breast cancer      |   |        |                   |                      |                                                          |                    |
| Unexposed          |   |        |                   |                      |                                                          |                    |
| Exposed – moderate |   |        |                   |                      |                                                          |                    |
| Exposed – severe   |   |        |                   |                      |                                                          |                    |
| Prostate cancer    |   |        |                   |                      |                                                          |                    |
| Unexposed          |   |        |                   |                      |                                                          |                    |
| Exposed – moderate |   |        |                   |                      |                                                          |                    |
| Exposed – severe   |   |        |                   |                      |                                                          |                    |
| Pancreatic cancer  |   |        |                   |                      |                                                          |                    |
| Unexposed          |   |        |                   |                      |                                                          |                    |
| Exposed – moderate |   |        |                   |                      |                                                          |                    |
| Exposed – severe   |   |        |                   |                      |                                                          |                    |
| Melanoma           |   |        |                   |                      |                                                          |                    |

## Analysis plan

Unexposed  
 Exposed – moderate  
 Exposed – severe  
 Keratinocyte cancer  
 Unexposed  
 Exposed – moderate  
 Exposed – severe  
 Lymphoma  
 Unexposed  
 Exposed – moderate  
 Exposed – severe  
 Multiple myeloma  
 Unexposed  
 Exposed – moderate  
 Exposed – severe  
 Leukaemia  
 Unexposed  
 Exposed – moderate  
 Exposed – severe  
 Meningioma  
 Unexposed  
 Exposed – moderate  
 Exposed – severe  
 Cancer of the brain, hypophysis,  
 corpus pineale and ductus  
 craniopharyngealis  
 Unexposed  
 Exposed – moderate  
 Exposed – severe  
 Spinal cord, cranial nerve or other  
 CNS tumours  
 Unexposed  
 Exposed – moderate  
 Exposed – severe

Estimated hazard ratios from Cox regression with time since index date as underlying timescale, stratified by matched set.

Unadjusted: No adjustment.

Mediation model: Adjusted additionally for time-varying lifestyle-related diseases.

**Table 4. Number of events, accumulated person-time, and HRs for cancer associated with eczema activity, Denmark**

|            | N | events | P-Y
at
risk | Rate
per
1,000 | Hazard ratio and 99%
confidence interval  |                    |
|------------|---|--------|-------------------|----------------------|----------------------------------------------------------|--------------------|
|            |   |        |                   |                      | Unadjusted                                               | Mediation
model |
| Any cancer |   |        |                   |                      |                                                          |                    |

## Analysis plan

- Unexposed
- Exposed – never active
- Exposed – <50% active
- Exposed –  $\geq 50\%$  active

### Lung cancer

- Unexposed
- Exposed – never active
- Exposed – <50% active
- Exposed –  $\geq 50\%$  active

### Breast cancer

- Unexposed
- Exposed – never active
- Exposed – <50% active
- Exposed –  $\geq 50\%$  active

### Prostate cancer

- Unexposed
- Exposed – never active
- Exposed – <50% active
- Exposed –  $\geq 50\%$  active

### Pancreatic cancer

- Unexposed
- Exposed – never active
- Exposed – <50% active
- Exposed –  $\geq 50\%$  active

### Melanoma

- Unexposed
- Exposed – never active
- Exposed – <50% active
- Exposed –  $\geq 50\%$  active

### Keratinocyte cancer

- Unexposed
- Exposed – never active
- Exposed – <50% active
- Exposed –  $\geq 50\%$  active

### Lymphoma

- Unexposed
- Exposed – never active
- Exposed – <50% active
- Exposed –  $\geq 50\%$  active

### Multiple myeloma

- Unexposed
- Exposed – never active
- Exposed – <50% active
- Exposed –  $\geq 50\%$  active

### Leukaemia

- Unexposed
- Exposed – never active
- Exposed – <50% active

## Analysis plan

Exposed –  $\geq 50\%$  active  
Meningioma  
Unexposed  
Exposed – never active  
Exposed –  $< 50\%$  active  
Exposed –  $\geq 50\%$  active  
Cancer of the brain, hypophysis,  
corpus pineale and ductus  
craniopharyngealis  
Unexposed  
Exposed – never active  
Exposed –  $< 50\%$  active  
Exposed –  $\geq 50\%$  active  
Spinal cord, cranial nerve or other  
CNS tumours  
Unexposed  
Exposed – never active  
Exposed –  $< 50\%$  active  
Exposed –  $\geq 50\%$  active

Estimated hazard ratios from Cox regression with time since index date as underlying timescale, stratified by matched set.

Unadjusted: No adjustment.

Mediation model: Adjusted additionally for time-varying lifestyle-related diseases.

7. As a subgroup analysis, we will stratify the results by variables listed below:

- Age (Table 5)
- Sex (Table 6)
- Asthma (Table 7)

**Table 5. Number of events, accumulated person-time, and HRs for cancer associated with eczema, Denmark, by age**

|                 | N | events | P-Y
at
risk | Rate
per
1,000 | Hazard ratio and 99%
confidence interval  |                    |
|-----------------|---|--------|-------------------|----------------------|----------------------------------------------------------|--------------------|
|                 |   |        |                   |                      | Unadjusted                                               | Mediation
model |
| Any cancer      |   |        |                   |                      |                                                          |                    |
| Age <18 years   |   |        |                   |                      |                                                          |                    |
| Unexposed       |   |        |                   |                      |                                                          |                    |
| Exposed         |   |        |                   |                      |                                                          |                    |
| Age 18–44 years |   |        |                   |                      |                                                          |                    |
| Unexposed       |   |        |                   |                      |                                                          |                    |

## Analysis plan

Exposed  
Age 45–64 years  
Unexposed  
Exposed  
Age >64 years  
Unexposed  
Exposed  
Lung cancer  
Age <18 years  
Unexposed  
Exposed  
Age 18–44 years  
Unexposed  
Exposed  
Age 45–64 years  
Unexposed  
Exposed  
Age >64 years  
Unexposed  
Exposed  
Breast cancer  
Age <18 years  
Unexposed  
Exposed  
Age 18–44 years  
Unexposed  
Exposed  
Age 45–64 years  
Unexposed  
Exposed  
Age >64 years  
Unexposed  
Exposed  
Prostate cancer  
Age <18 years  
Unexposed  
Exposed  
Age 18–44 years  
Unexposed  
Exposed  
Age 45–64 years  
Unexposed  
Exposed  
Age >64 years  
Unexposed  
Exposed  
Pancreatic cancer  
Age <18 years

---

## Analysis plan

---

|                     |
|---------------------|
| Unexposed           |
| Exposed             |
| Age 18–44 years     |
| Unexposed           |
| Exposed             |
| Age 45–64 years     |
| Unexposed           |
| Exposed             |
| Age >64 years       |
| Unexposed           |
| Exposed             |
| Melanoma            |
| Age <18 years       |
| Unexposed           |
| Exposed             |
| Age 18–44 years     |
| Unexposed           |
| Exposed             |
| Age 45–64 years     |
| Unexposed           |
| Exposed             |
| Age >64 years       |
| Unexposed           |
| Exposed             |
| Keratinocyte cancer |
| Age <18 years       |
| Unexposed           |
| Exposed             |
| Age 18–44 years     |
| Unexposed           |
| Exposed             |
| Age 45–64 years     |
| Unexposed           |
| Exposed             |
| Age >64 years       |
| Unexposed           |
| Exposed             |
| Lymphoma            |
| Age <18 years       |
| Unexposed           |
| Exposed             |
| Age 18–44 years     |
| Unexposed           |
| Exposed             |
| Age 45–64 years     |
| Unexposed           |
| Exposed             |
| Age >64 years       |

---

## Analysis plan

---

|                                                                                     |
|-------------------------------------------------------------------------------------|
| Unexposed                                                                           |
| Exposed                                                                             |
| Multiple myeloma                                                                    |
| Age <18 years                                                                       |
| Unexposed                                                                           |
| Exposed                                                                             |
| Age 18–44 years                                                                     |
| Unexposed                                                                           |
| Exposed                                                                             |
| Age 45–64 years                                                                     |
| Unexposed                                                                           |
| Exposed                                                                             |
| Age >64 years                                                                       |
| Unexposed                                                                           |
| Exposed                                                                             |
| Leukaemia                                                                           |
| Age <18 years                                                                       |
| Unexposed                                                                           |
| Exposed                                                                             |
| Age 18–44 years                                                                     |
| Unexposed                                                                           |
| Exposed                                                                             |
| Age 45–64 years                                                                     |
| Unexposed                                                                           |
| Exposed                                                                             |
| Age >64 years                                                                       |
| Unexposed                                                                           |
| Exposed                                                                             |
| Meningioma                                                                          |
| Age <18 years                                                                       |
| Unexposed                                                                           |
| Exposed                                                                             |
| Age 18–44 years                                                                     |
| Unexposed                                                                           |
| Exposed                                                                             |
| Age 45–64 years                                                                     |
| Unexposed                                                                           |
| Exposed                                                                             |
| Age >64 years                                                                       |
| Unexposed                                                                           |
| Exposed                                                                             |
| Cancer of the brain, hypophysis,
corpus pineale and ductus
craniopharyngealis |
| Age <18 years                                                                       |
| Unexposed                                                                           |
| Exposed                                                                             |
| Age 18–44 years                                                                     |

---

## Analysis plan

---

|                                     |
|-------------------------------------|
| Unexposed                           |
| Exposed                             |
| Age 45–64 years                     |
| Unexposed                           |
| Exposed                             |
| Age >64 years                       |
| Unexposed                           |
| Exposed                             |
| Spinal cord, cranial nerve or other |
| CNS tumours                         |
| Age <18 years                       |
| Unexposed                           |
| Exposed                             |
| Age 18–44 years                     |
| Unexposed                           |
| Exposed                             |
| Age 45–64 years                     |
| Unexposed                           |
| Exposed                             |
| Age >64 years                       |
| Unexposed                           |
| Exposed                             |

---

Estimated hazard ratios from Cox regression with time since index date as underlying timescale, stratified by matched set.

Unadjusted: No adjustment.

Mediation model: Adjusted additionally for time-varying lifestyle-related diseases.

---

**Table 6. Number of events, accumulated person-time, and HRs for cancer associated with eczema, Denmark, by sex**

---

|             | N | events | P-Y
at
risk | Rate
per
1,000 | Hazard ratio and 99%
confidence interval  |                    |
|-------------|---|--------|-------------------|----------------------|----------------------------------------------------------|--------------------|
|             |   |        |                   |                      | Unadjusted                                               | Mediation
model |
| Any cancer  |   |        |                   |                      |                                                          |                    |
| Female      |   |        |                   |                      |                                                          |                    |
| Unexposed   |   |        |                   |                      |                                                          |                    |
| Exposed     |   |        |                   |                      |                                                          |                    |
| Male        |   |        |                   |                      |                                                          |                    |
| Unexposed   |   |        |                   |                      |                                                          |                    |
| Exposed     |   |        |                   |                      |                                                          |                    |
| Lung cancer |   |        |                   |                      |                                                          |                    |
| Female      |   |        |                   |                      |                                                          |                    |
| Unexposed   |   |        |                   |                      |                                                          |                    |
| Exposed     |   |        |                   |                      |                                                          |                    |
| Male        |   |        |                   |                      |                                                          |                    |

## Analysis plan

Unexposed  
Exposed  
Breast cancer  
Female  
Unexposed  
Exposed  
Male  
Unexposed  
Exposed  
Prostate cancer  
Female  
Unexposed  
Exposed  
Male  
Unexposed  
Exposed  
Pancreatic cancer  
Female  
Unexposed  
Exposed  
Male  
Unexposed  
Exposed  
Melanoma  
Female  
Unexposed  
Exposed  
Male  
Unexposed  
Exposed  
Keratinocyte cancer  
Female  
Unexposed  
Exposed  
Male  
Unexposed  
Exposed  
Lymphoma  
Female  
Unexposed  
Exposed  
Male  
Unexposed  
Exposed  
Multiple myeloma  
Female  
Unexposed  
Exposed

## Analysis plan

Male  
     Unexposed  
     Exposed  
 Leukaemia  
     Female  
         Unexposed  
         Exposed  
     Male  
         Unexposed  
         Exposed  
 Meningioma  
     Female  
         Unexposed  
         Exposed  
     Male  
         Unexposed  
         Exposed  
 Cancer of the brain, hypophysis,  
 corpus pineale and ductus  
 craniopharyngealis  
     Female  
         Unexposed  
         Exposed  
     Male  
         Unexposed  
         Exposed  
 Spinal cord, cranial nerve or other  
 CNS tumours  
     Female  
         Unexposed  
         Exposed  
     Male  
         Unexposed  
         Exposed

Estimated hazard ratios from Cox regression with time since index date as underlying timescale, stratified by matched set.

Unadjusted: No adjustment.

Mediation model: Adjusted additionally for time-varying lifestyle-related diseases.

**Table 7. Number of events, accumulated person-time, and HRs for cancer associated with eczema, Denmark, by presence of asthma**

|  | N | events | P-Y
at
risk | Rate
per
1,000 | Hazard ratio and 99%
confidence interval  |                    |
|--|---|--------|-------------------|----------------------|----------------------------------------------------------|--------------------|
|  |   |        |                   |                      | Unadjusted                                               | Mediation
model |

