## Analysis plan

### *Eczema exposed*

- Persons with a diagnosis of atopic eczema (ICD-8: 691; ICD-10: DL20) in the Danish National Patient Registry between 1 Jan 1977 and 10 February 2018.
- We include all primary and secondary diagnoses for eczema from admissions, hospital outpatient clinics and emergency rooms in the Danish National Patient Registry, including ongoing contacts (that is, persons who at the end of study period are in active follow-up in a hospital outpatient clinic).
- Index date = The earliest hospital record for atopic eczema (date of admission or first outpatient appointment).
- Only persons who are born in Denmark and living in Denmark on the index date (i.e. date of first record for eczema).

For the current study, we will further restrict the study population as follows:

- We will exclude eczema patients (together with their matched comparators) identified by an ICD-8 diagnosis recorded together with an additional (“modification”) code indicating that it potentially an uncertain/unverified/working diagnosis (c\_diagmod=1–7).
- We will exclude patients (together with their matched comparators) with inconsistencies in registration of status and residence in the Civil Registration System (recorded as alive but not living in Denmark but without an emigration date), as we assume that these patients are not living in Denmark and thus not eligible.
- To ensure that we have at least 1 year of registration history from included registries (except the prescription registry), we will only include patients (together with their matched comparators) with index date on 1 January 1982 or later. In the subanalysis on severity and in a sensitivity analysis, we restrict to those diagnosed on 1 January 1996 or later in order to ensure one year of registration history in all databases.
- To ensure at least 1 year of follow-up after start of eligible follow-up (available until 30 June 2017), we will include eczema patients until 30 June 2016.
- We will exclude eczema patients (together with their matched comparators) with a record for any cancer (except non-melanoma skin cancer) before or on index date (see Table 2). That is, we will not only exclude those with history of the cancer outcome of interest. However, in analyses of non-melanoma skin cancer specifically, we will exclude those with previous history of this cancer as well.

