### *Unexposed cohort*

- Up to 10 persons matched to each eczema patient by sex and birth year.
- Comparators have to: (1) be born in Denmark, (2) be alive and living in Denmark on the on index date of their matched eczema-exposed individual (i.e. first hospital eczema diagnosis), and (3) have no previous diagnosis of eczema.
- Index date = The same index date as their matched eczema-exposed individual

As with eczema patients, we will additionally apply the following restrictions:

- We will exclude matched comparators with inconsistencies in registration of status and residence in the Civil Registration System (recorded as alive but not living in Denmark but without an emigration date), as we assume that these patients are not living in Denmark and thus not eligible.
- We will exclude comparators with any cancer (except non-melanoma skin cancer) before or on index date (see Table 2). That is, we will not only exclude those with history of the cancer outcome of interest. However, in analyses of non-melanoma skin cancer specifically, we will exclude those with previous history of this cancer as well.

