### Covariables

We will include various variables, shown in table 3. With the exception of socioeconomic variables, variables are time-updated. Thus, people will contribute person-time in the unexposed category for a given variable until they fulfill the definition for the condition/treatment, after which they will contribute in the exposed category for the remaining follow-up.

**Table 3.** Covariables

| ICD-8 | ICD-10 | Other codes in patient registry | ATC | Notes |
|-------|--------|---------------------------------|-----|-------|
|-------|--------|---------------------------------|-----|-------|

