|                                                                                                    |                  | "DC94" "DC95"
"DC81" "DC82"
"DC83" "DC84"
"DC85" "DC86"
"DC88" "DC96"           |                                        |
| Use of oral corticosteroids                                                                        |                  | "H02AB" and
DOSFOR M "TAB"
or
"TABMO D"                                            | Any prescription excluding injections. |
| Systemic treatment for eczema (cyclosporine, azathioprine, mycophenolate, methotrexate, dupilumab) | Procedure codes: | "L04AX0 1"
"BOHJ18 B8"
"BWHB83 3"
"BWAH1 15"
"BOHJ20"
"BOHJ22"
"D11AH0 5" |                                        |
| Asthma                                                                                             | "493"            | "DJ45" "DJ46"                                                                               |                                        |

Note: All subcodes are included unless otherwise stated; all types of contacts (inpatient, outpatient and emergency) and both primary and secondary diagnoses should be considered. Use admission/prescription/record date for all variables.

aBaseline information only

bDocumentation is available here:

<https://www.dst.dk/da/Statistik/dokumentation/Times/forskningsservice/efalle>

<https://www.dst.dk/da/Statistik/dokumentation/Times/cpr-oplysninger/c-faelle-id>

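### Table 7 splits by hospital-coded asthma, which is likely to be recorded more completely and with a different severity mix in eczema patients than in comparators, so apparent effect modification could be a recording artefact

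*Protocol*

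**What the plan says.** The secondary aim in the Protocol (Objectives, Specific Aims and Rationale) names coexisting asthma among the factors on which cancer risk may depend. Item 7 under Subgroup analyses answers it with Table 7: "HRs for cancer associated with eczema, Denmark, by presence of asthma".

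The asthma row of the covariable table lists ICD-8 493 and ICD-10 DJ45 and DJ46, and shows no drug code. The note below that table says "all types of contacts (inpatient, outpatient and emergency) and both primary and secondary diagnoses should be considered". The Covariables section adds "With the exception of socioeconomic variables, variables are time-updated", and a person stays positive after the first qualifying record.

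The cohorts enter differently:

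- Eczema exposed: "Index date = The earliest hospital record for atopic eczema (date of admission or first outpatient appointment". On which records count: "We include all primary and secondary diagnoses for eczema from admissions, hospital outpatient clinics and emergency rooms".
- Unexposed cohort: "Up to 10 persons matched to each eczema patient by sex and birth year". Comparators must be Danish-born, without previous eczema, and must "be alive and living in Denmark on the on index date of their matched eczema-exposed individual". For timing: "Index date = The same index date as their matched eczema-exposed individual".

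No hospital contact is required of comparators, and contact is not a matching factor.

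**The concern.** The asthma rule has the same wording for both cohorts but not the same opportunity to operate. Each eczema patient has at least one hospital contact, on day 0, and may have further eczema contacts. At any of these, asthma that is otherwise managed outside hospital can be added as a secondary code. A comparator with the same asthma is recorded only if something else brings him or her to hospital.

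The asthma stratum may therefore set eczema patients with a broad range of asthma against comparators whose recorded asthma is, on average, of another severity. If cancer risk rises with asthma severity, the eczema HR in that stratum is distorted while the no-asthma HR hardly moves. The contrast between the two would then be read as an answer to the secondary aim.

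No planned analysis checks for this. Table 1 shows baseline asthma by cohort, but a higher share among eczema patients could be true comorbidity or better recording. Items 16 and 17 examine ascertainment for skin cancer; the asthma subgroup has no counterpart.

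**Working it through.** The Protocol gives no asthma prevalence, capture rate or event count, so there is no stated figure to reproduce. The calculation shows only what unequal capture could do.

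**From the Protocol:** the asthma codes, the any-position rule, entry by hospital contact for the exposed only, and 99% confidence intervals (z = 2.576).

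**Assumed:** the true eczema HR is 1 in every asthma class. True asthma prevalence *p* is 20% in eczema patients and 8% in comparators. Of true asthma, 20% is severe, and severe asthma is recorded with probability 0.9 in both cohorts. The cancer rate ratio against no asthma is 1.0 for mild and *r* for severe asthma. The probability *c* that mild asthma is recorded varies by cohort.

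**Rate in recorded asthma**, relative to no asthma (*p* cancels):

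R_A = (0.8c × 1.0 + 0.2 × 0.9 × r) / (0.8c + 0.2 × 0.9)

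**Rate in recorded no asthma:**

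R_N = [(1 − p) + 0.8p(1 − c) + 0.2p × 0.1 × r] / [(1 − p) + 0.8p(1 − c) + 0.2p × 0.1]

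The apparent HR in each stratum is the exposed value divided by the comparator value.

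**Worked case, c = 0.5 vs 0.2, r = 2.0:**

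- Asthma, exposed: (0.40 + 0.36) / 0.58 = 1.310
- Asthma, comparators: (0.16 + 0.36) / 0.34 = 1.529
- HR in the asthma stratum: 1.310 / 1.529 = 0.857
- No asthma, exposed: 0.888 / 0.884 = 1.0045
- No asthma, comparators: 0.9744 / 0.9728 = 1.0016
- HR in the no-asthma stratum: 1.003
- Ratio of HRs: 0.857 / 1.003 = 0.854

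**Ratio of HRs (asthma / no asthma):**

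| Mild asthma recorded, exposed vs comparators | r = 1.0 | r = 1.2 | r = 1.5 | r = 2.0 |
|---|---|---|---|---|
| 30% vs 30% | 1.00 | 1.00 | 1.00 | 1.00 |
| 50% vs 20% | 1.00 | 0.96 | 0.91 | 0.85 |
| 60% vs 10% | 1.00 | 0.93 | 0.84 | 0.75 |

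The no-asthma HR lies between 1.00 and 1.02 in every run. With true prevalence 8% in both cohorts, the 50% vs 20% row is 0.96, 0.91 and 0.86, so the effect does not depend on eczema patients having more asthma. Giving mild asthma some excess risk stays inside the range: with rate ratios of 1.2 (mild) and 2.0 (severe) the ratio is 0.88 at 50% vs 20% and 0.80 at 60% vs 10%, and 0.98 with equal capture.

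**What would reverse it.** Suppose the severe share of true asthma among eczema patients is *q* instead of 20%, because asthma contacts with secondary eczema bring people into that cohort. The asthma-stratum HR returns to 1 when recorded severe to recorded mild is the same in both cohorts.

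- At 50% vs 20%: 0.9q / [0.5(1 − q)] = 0.18 / 0.16 = 1.125, so q = 0.5625 / 1.4625 = 38%.
- At 60% vs 10%: 0.9q / [0.6(1 − q)] = 0.18 / 0.08 = 2.25, so q = 1.35 / 2.25 = 60%.

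Above these shares the apparent HR among asthmatics exceeds 1.

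**Precision for scale.** Ignoring the matching, each 99% limit lies a factor exp(2.576 × √(1/d₁ + 1/d₀)) from the estimate: 1.90 with 20 exposed and 80 unexposed events, 1.33 with 100 and 400. These event counts are illustrative.

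**The case against.** A reader might infer that mild asthma is captured in the exposed only. The Protocol does not support that. The same time-updated rule covers comparators, and any hospital contact of theirs can carry a secondary asthma code. With zero capture of mild asthma in comparators (60% vs 0%) the ratios fall to 0.88, 0.76 and 0.63; these are an extreme, not an estimate. What remains supported is more complete recording in the exposed.

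A reader might also infer that the bias must pull the asthma HR downward. That does not follow either. Eczema on a secondary code from an admission or emergency contact is enough for entry, so a person admitted for asthma can become an eczema patient and enrich that cohort with severe asthma. The break-even shares above show that this could offset or reverse the dilution.

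The consequences have limits too. Subgroup analyses may be confined to overall cancer if power is low, and results with fewer than 20 events will generally not be published, so a lung-cancer result by asthma may never appear. The mediation-model column of Table 7 adjusts for time-varying chronic obstructive pulmonary disease, which covers part of any smoking-related route. With few events, a distortion of 4% to 15% would be hard to see within 99% intervals.

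These points limit the size and certainty of the concern. They do not make the recording equal, and no planned analysis would show whether it is.

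**Conclusion.** The concern holds as a possible recording artefact of unknown size and direction. The definitions give the exposed a guaranteed opportunity for asthma to be coded and give comparators none, in the only analysis serving the asthma part of the secondary aim. Under the stated assumptions the spurious ratio of HRs is about 0.75 to 0.96. It is 1.00 if cancer risk does not vary with asthma severity, and above 1 if enough severe asthma enters through secondary eczema codes. Nearly all of the distortion sits in the asthma stratum. Capture rates, severity shares and rate ratios are all assumptions; none comes from the Protocol. This justifies a check before effect modification is claimed, not a conclusion that Table 7 will be wrong.

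**What to change.** Keep Table 7 as planned. Beside it, at least for any cancer, add a version in which a person counts as having asthma only when 493, DJ45 or DJ46 is the primary diagnosis of a contact, with the same rule in both cohorts. The plan already uses diagnostic position to define severe eczema. State effect modification by asthma only if both versions point the same way.

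Do not also require that the asthma contact carry no eczema code. Comparators have no previous eczema and are censored at an eczema diagnosis, so that condition would fall almost entirely on the exposed and create an asymmetry of its own.

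The cost is one code-list rule and one rerun. The added version has a smaller asthma stratum and wider 99% intervals. It addresses secondary coding of asthma at eczema contacts; it does not remove entry to the eczema cohort through an asthma contact, so agreement between the versions supports effect modification without proving it.
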